#### Physical examination

The examination will be carried out at every visit and will include:

- Lung auscultation
- Assessment of the visible mucous membranes of the upper respiratory tract
- Palpation and assessment of lymph nodes
- Evaluation of the abdominal organs and size of the liver and spleen (by palpation, without instrumental examination)
- Evaluation of the general condition, skin, eyes, musculoskeletal system, ENT, nervous system, gastro-intestinal tract, urinary track system.

#### Vital signs assessment

- Measurement of the body temperature
- Measurement of the respiration rate,
- Measurement of the blood pressure,

- Measurement of the heart rate

The assessment will be carried out at every visit. Subjects should be resting for at least 5 minutes prior to having vital sign measurements obtained in sitting position.

#### 12-lead ECG

ECG will be done in supine position at Screening and End-of-study Visits. Subjects should be resting for at least 5 minutes prior to each ECG measurement.

#### Pregnancy test (in women with childbearing potential)

Pregnancy test will be performed upon Screening and at Visit 5 (upon treatment completion). It will be a standard urine test for  $\beta$ -HCG (test strip).

### **4.2 Description of the Measures Taken to Minimize/Avoid Bias**

#### **4.2.1 Randomization**

After consenting to participate in the study and completing the baseline assessment, eligible participants will be randomized to receive either the NeuroAiD II™ (MLC901) or placebo using 1:1 stratified permuted block randomization. This approach will help to stratify by study center, time since injury [1-3 months/4-12 months] and gender. Time since injury between 3 and 4 months will be stratified to 1-3 months. Centralized stratified permuted block randomization will be done using Interactive Web Response System (IWRS). The randomization number will be generated by the system automatically after the investigator enters the patient data into the system. The study team, including the biostatistician, will be un-blinded only after database has been locked.

After the patient signs the ICF at the screening visit, he/she will be assigned the screening number that is assigned in the order of enrolment.

The randomization code will be assigned to each patient that passed the screening and was found eligible.

The randomization code of each patient will be recorded in the source records and the patient's Case Report Form (CRF). If the patient decides to leave the study or does not complete the study for any reason, then his randomization code should not be reused.

#### **4.2.2 Blinding**

This study is double-blind i.e. the patients and the investigators will not know the treatment assignments. Accordingly, the primary and secondary packaging of the IP and placebo will be blinded. The efficacy and safety outcomes will be defined based on the blinded analysis of data.

Information on unblinding is provided in Section 4.7.

### **4.3 Description of the Study Treatments**

*Table 4.1. Study treatments.*

| Investigational Drugs | Dose/Potency | Dose Frequency | Route of Administration | Treatment period | Use |
|-----------------------|--------------|----------------|-------------------------|------------------|-----|
|-----------------------|--------------|----------------|-------------------------|------------------|-----|

|                       |                                            |                     |        |          |            |
|-----------------------|--------------------------------------------|---------------------|--------|----------|------------|
| NeuroAiD II™ (MLC901) | Standard dose of 2 capsules (0.4g/capsule) | 3x/day for 6 months | orally | 6 months | Study drug |
| Placebo               | 2 capsules (0.4g/capsule)                  | 3x/day for 6 months | orally | 6 months | Control    |

The experimental and control capsules will be presented in blister packs prepared by Moleac Pte Ltd and will have identical appearance.

All participants will continue to receive standard medical care, without any changes in medical treatment recorded.

#### **4.4 Expected Duration of Subject Participation, and a Description of the Sequence and Duration of All Study Periods, Including Follow-up**

The total duration of a patient's participation in this study will not exceed 314 days starting with the screening visit and finishing with the final End-of-Study visit or Early Termination visit.

The study will consist of 3 periods:

- **Screening** (Day -14 ... Day -1)
- **Treatment period** (6 months, Day 1 – Day 180±14), during which patients will daily receive an oral dose of IP or placebo
- **Follow-up period** (3 months, Day 180±14 – Day 270±30), after which final efficacy assessment will be performed

#### **4.5 Description of the "Stopping Rules" or "Discontinuation Criteria" for Individual Subjects, Parts of Study and Entire Study**

The Sponsor may suspend the study at any time based on any reasons that include, but are not limited to, safety, ethics, or administrative issues. The Sponsor can terminate the study at any time if the aim and objectives of the study are not met. The Sponsor should inform the investigator or the leadership of the study center about the study suspension or termination in writing. If the study is suspended or terminated because of a safety issue, the Sponsor shall notify the investigators, regulatory authorities, and the Ethics Committees immediately.

#### **4.6 Accountability Procedures for the Investigational Product(s), Including the Placebo and Comparator**

Designated clinical staff will be responsible for receipt, storage, dispensing and accounting of study drugs according to Good Clinical Practice (GCP) and site's SOPs. The study drugs will be placed under appropriate storage conditions in an area with controlled access. Before dosing, the IP will be individually packed and labeled for each subject and period at the trial site and checked prior to IP administration.

The investigator must ensure that the Sponsor-supplied drug is used in accordance with the protocol and is dispensed only to subjects enrolled in the study. Drug supplies will be counted and reconciled at the site before being returned to the Sponsor. To document appropriate use of Sponsor-supplied drug, the Investigator will maintain records of all Sponsor-supplied drug delivery to the site and use by each subject. If any dispensing errors or discrepancies are discovered, the sponsor must be notified immediately.

The following information will be recorded by the Investigator: protocol number and title, name of Investigator, site identifier and number, description of Sponsor-supplied drugs, expiry date and amount dispensed, and the date and amount returned to the site by the subject. All study drug not returned to the site by a subject must be investigated by the site and appropriately documented.

To make the IP accountability process clearer, the Investigator will ask the subjects to fill the IP administration diary during the treatment period. The specially prepared IP administration diaries will be handled to subjects on Day 1.

#### **4.7 Maintenance of Study Treatment Randomization Codes and Procedures for Breaking Codes**

The double blinding will be maintained during the whole study. The randomization code of a patient can be broken in case of:

- Occurrence of an insured event if the assigned treatment must be revealed for qualification of the case
- Decision of the Sponsor
- Written requirement of the LEC that oversees the study

The patient's randomization code may be disclosed prematurely (during the clinical trial) in order to ensure patient safety, i.e. in the case of AE and in the case when information about the receiving treatment influences the further treatment tactics.

Unblinding is done using IWRS (Unblinding section). If possible, before breaking the code, the Investigator should inform the Study Sponsor and monitor about the need to disclose the code. The Investigator must make at least 3 attempts to contact the Study Sponsor / responsible monitor. In any case, after breaking the code the Investigator must inform the Sponsor and the monitor about it. The fact of code disclosure should be documented in the source documents.

A complete list of all the screening/randomization numbers used in the study and the corresponding therapy is a confidential document that is kept by an authorized representative and is used to monitor the conduct of the study.

The investigator must maintain the records with information on patient numbers. These records are stored in compliance with the rules applicable to confidential documents.

#### **4.8 Identification of Any Data to be Recorded Directly on the Electronic CRF (eCRFs)**

In this study, all data will be recorded in the primary documentation before entry into the CRF. At the end of each study participant visit, data of the visit including all scores will be entered into the CRF. CRF completion must be legible and complete. CRF must be kept current to reflect participant status at each phase during the course of the study. The investigator will be responsible for retaining all records pertaining to the study as specified in the contract.

## 5 SELECTION AND WITHDRAWAL OF SUBJECTS

This clinical trial will include 182 adults 18-65 years of age who experienced a mild TBI in the past 1 to 12 months and have cognitive functioning difficulties as indicated by a score of >30 on the Cognitive Failures Questionnaire (consistent with criteria in the pilot study). Eligible participants will be randomized to receive either NeuroAiD II™ (MLC901) or matching placebo.

### 5.1 Subject Inclusion Criteria

In order to participate in the study patient should meet the following inclusion criteria:

1. Patient with mild TBI, which occurred 1-12 months prior enrolment to the study. Mild TBI is defined as an external force from an incident causing injury to the brain and resulting in an altered level of consciousness. The mTBI diagnosis should be documented. Mild TBI is evidenced by any of the following:
  - best Glasgow Coma Score 13-15 as assessed on scene, on admission and over next 3 days
  - loss of consciousness for up to 30 minutes
  - dazed and confused at the time of injury or post-TBI amnesia of < 24 hours duration
2. Patient experiencing cognitive impairment following injury, determined by the Cognitive Failures Questionnaire score >30 (consistent with criteria in the pilot NeuroAiD II™ study (21)).
3. Adult male or female patients aged 18-65 years.
4. The patient signed an Informed Consent form (ICF) for participation in this study before initiation of study procedures.
5. The patient can understand all protocol requirements, perform the study procedures, and agree to all limitations specified in the protocol.
6. The patient agrees to use adequate contraception methods (for women of child-bearing potential)

### 5.2 Subject Exclusion Criteria

Patient will not be included in the study, if any of the following criteria is present:

1. Moderate or Severe TBI, determined by best Glasgow Coma Score of <13 (as assessed on scene, on admission and over next 3 days), or injury requiring neurosurgery (even if surgery was not done)
2. Co-existing severe co-morbidity, including end stage renal failure, spinal cord injury, significant substance abuse, severe liver disease, significant mental illnesses, diabetes requiring insulin injections, severe agitation, advanced cancer or other severe conditions with life expectancy of less than 5 years. The decision on significance of the comorbidity for inclusion/exclusion from current study is made by the Investigator.
3. Current participation in another clinical trial within 30 days
4. Women who are pregnant or who have a positive urine pregnancy test or breast-feeding
5. Not fluent in Russian language or have aphasia/dysphasia
6. No documented evidence of mTBI

7. Known allergy to MLC901/NeuroAiD II™ or any of its component ingredients
8. Other medical condition which in the opinion of the Principal Investigator would place undue risk on the patient if included in the trial or likely to interfere with NeuroAiD II™
9. History of psychic (including depressive) disorders, physical and other factors that do not allow for adequate self-assessment of one's behaviour and for compliance with the protocol requirements, including history of psychiatric disorders.
10. Use of hormonal contraceptives, either oral or implant.

### 5.3 Contraception

Females in this study will be of child-bearing potential (WOCBP) and not of child-bearing potential. Females considered to be not of child-bearing potential, are:

- Surgically sterile (i.e. both ovaries removed, uterus removed or bilateral tubal ligation) and/or
- Post-menopausal (no menstrual period for at least 12 consecutive months without any other medical cause).

A female subject is considered to be a WOCBP if she is physically capable of becoming pregnant and does not fulfil any of the above-mentioned criteria

Prior to participating in the study, all patients should be informed about the importance of preventing an unwanted pregnancy while participating in the study and the potential risk factors for an unwanted pregnancy.

Subjects and their sexual partner must use an acceptable single- or double method of contraception from the Screening visit until completion of the study. The possibility of known or unknown drug interactions between the hormonal contraceptives and the investigational medicinal product always exist. Moreover, there is a possibility that the investigational product may lessen the effectiveness of a hormonal contraceptive agent. Hence female subjects with childbearing potential using hormonal contraceptives will not be included in the study.

Acceptable single- or double-methods of contraception are presented below:

*Table 5.1. Acceptable Effective Methods of Contraception*

| Single-method                                                                                                                   | Double-method (must use at least two of them)                                                                                                  |                                                                                                          |
|---------------------------------------------------------------------------------------------------------------------------------|------------------------------------------------------------------------------------------------------------------------------------------------|----------------------------------------------------------------------------------------------------------|
| 
 
• Surgically sterile;
 
• Postmenopausal;
 
• Remain abstinent.
 
 | 
 
• Diaphragm;
 
• Cervical cap;
 
• Vaginal sponge;
 
• Non-hormonal IUD
 
 | 
 
• Condom;
 
• Spermicide;
 
• Vasectomy.
 
 |

The study subjects should consent to use the methods of contraception described above throughout the study period or to complete abstinence during the study period.

### 5.4 Subject Withdrawal Criteria

1. The patient withdraws the Informed Consent.

2. Patient's pregnancy: patients will be recommended to use effective contraception methods during the study, however if pregnancy occurs during the study, the IP/placebo treatment and other study procedures concerning the pregnant patient are cancelled, patient's pregnancy will be monitored up to pregnancy completion if the patient agrees.
3. Any medical condition of the patient that requires withdrawal of that patient from the study, as judged by the Investigator.
4. Patient lost to follow-up.

The investigator can withdraw a subject from the study if any of the withdrawal criteria are met. Patients are free to withdraw from the study at any time upon request, without any consequence. Patients should be listed as having withdrawn consent only when they no longer wish to participate in the study and no longer authorize the investigators to make efforts to continue collection of the outcomes. Every effort should be made to encourage patients to remain in the study for the duration of the planned outcome assessments. The patients should be told that their data are important for the scientific research, even after they discontinue the drug product.

The participant should no longer be contacted regarding the study after notification of withdrawal.

A subject will be considered lost to follow-up if he or she fails to appear for a follow-up assessment and cannot be contacted with good effort. These efforts will be documented in the subject's record. If not a single dose of the IP/comparator was taken by the patient, and he/she left the study for any reason, then further follow-up is cancelled, and his/her data are not included in the statistical analysis.

If the patient decides to leave the study or does not complete the study for any reason, then his randomization code should not be reused.

Unless the patient withdraws consent, those who discontinue the IP early remain in the study, if possible, for further collection of outcomes. The reason for discontinuation of the IP should be documented in the CRF.

The Investigator submits the data on the withdrawn patients to the Sponsor, local Principal Investigator and the monitor of the study within 24 hours in a report that includes the patient's status at the end of the study, as follows:

1. *Completed the study.*
2. *Did not complete the study because of:*
  - Any condition of the patient that requires withdrawal of that patient from the study, as judged by the investigator
  - The patient wished to leave the study
  - The patient lost to follow-up
  - Pregnancy
  - Other reasons (specify)

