## **5.6 Follow-up of the Withdrawn Patients**

The subjects that were withdrawn from the study because of an AE/SAE will be followed until the AE/SAE is resolved or the patient is stabilized.

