#### **8.3.1.2 Reporting of Pregnancy**

While pregnancy is not considered to be an AE or SAE, any pregnancy complication or elective termination of a pregnancy will be reported as an AE or SAE. A spontaneous abortion is always considered to be an SAE and will be reported as such. In situation when pregnancy occurs during study participation, it should be reported to Atlant Clinical medical monitor (for Sponsor

informing) within 24 hours using the procedure described for SAE reporting. Pregnancy should be recorded on the eCRF and source documents, a specialized Pregnancy Form should be filled.

If a female study participant is pregnant, then further IP intake and all study procedures should be cancelled. The female patient who becomes pregnant during the study will be followed using a Pregnancy Form until the outcome of the pregnancy is known.

Any pregnancies in the partner of a male study participant during the study should also be recorded following authorization from the subject's partner, withdrawal of the male study participant from the study is not required. Pregnancy of the male study participant's partner should also be followed using Pregnancy Form.

For both female subjects and partners of male subjects information about SAEs that occurred during pregnancy with the mother and/or fetus or child should be transmitted to the Sponsor also in case of Study discontinuation.

Pregnancy outcome, including any premature termination, must be reported to the Sponsor. An evaluation after the birth of the child should also be conducted.

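### Section 5.4 does not keep stopping the IP apart from leaving the study, so month-6 scores can be lost for reasons that may relate to treatment

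*Protocol*

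**What the plan says.** Section 5.4 of the protocol carries two kinds of instruction.

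**Retention.** Unless consent is withdrawn, "those who discontinue the IP early remain in the study, if possible, for further collection of outcomes". The section also defines withdrawal of consent narrowly and asks sites to encourage patients to stay for the planned assessments even when they are off the drug.

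**Exit.** All four listed criteria are grounds for leaving the study. Criterion 3 is "Any medical condition of the patient that requires withdrawal of that patient from the study, as judged by the Investigator". Criterion 2 says that in pregnancy "the IP/placebo treatment and other study procedures concerning the pregnant patient are cancelled". The criteria are permissive: "The investigator can withdraw a subject from the study if any of the withdrawal criteria are met". The status list that closes 5.4 names a medical condition and pregnancy among the reasons for not completing the study. The section also bars further study contact once a withdrawal has been notified.

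Elsewhere:

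- Section 5.6: "The subjects that were withdrawn from the study because of an AE/SAE will be followed until the AE/SAE is resolved or the patient is stabilized".
- Section 8.3.1.2: "If a female study participant is pregnant, then further IP intake and all study procedures should be cancelled".
- The synopsis repeats the four criteria without the retention sentence.
- Section 4.5 promises, in its title, discontinuation criteria for individual subjects, but its text covers only suspension or termination of the study by the sponsor.

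**The concern.** The retention sentence names one exception, withdrawal of consent. The other passages end participation, or study procedures, for patients who have not withdrawn consent. No category exists for a patient who comes off the capsules but stays under observation, beyond that one sentence.

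The primary endpoint is the change in complex attention at month 6. A patient who leaves on, say, Day 40 has an Early-Termination visit then (section 4.1), which gives a Day 40 score and no Day 180 score. Section 9.7 puts every randomized patient in the ITT population, section 9.5 leaves missing values unfilled in the primary analysis, and section 5.5 rules out replacement. The mixed model in 9.1.2 uses all timepoints, so it in effect predicts the absent month-6 value from the patient's earlier scores and from the patients who stayed. That is sound if the loss is at random given the observed data. It is less safe if patients leave because of tolerability or health and this happens more in one arm.

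**Working it through.** **1. The passages side by side**

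| Situation, consent not withdrawn | Retention rule (5.4) | Other passages | Relation |
|---|---|---|---|
| Pregnancy | Stays, if possible | 5.4 criterion 2 and 8.3.1.2: IP and study procedures cancelled | Direct conflict |
| Medical condition | Stays, if possible | 5.4 criterion 3 and the status list: study exit at the investigator's judgement | Compatible only if exit is confined to conditions that require it; no guide to which these are |
| AE or SAE | Stays, if possible | Not a listed criterion in 5.4; 5.6 presupposes study withdrawal for this reason | Open to differing site practice |

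**2. The plan's own figures**

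Inputs from section 9.2: difference 10 (absolute size), SD 20, two-sided 5%, power 80%, allocation 1:1, 30% dropout.

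- Standardized difference 10/20 = 0.5. The two-sample t-test needs 63.8, so 64 per arm (128 in total). Power at 64 per arm is 80.1%. The stated 128 is reproduced.
- 128/0.70 = 182.9, against the stated 182; 182 × 0.70 = 127.4 evaluable. This agrees to within one patient.

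The point contests none of these numbers. The 30% allowance restores sample size; it gives no protection against selective loss.

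**3. Possible size of the bias, under assumptions**

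Let x be the excess share of the MLC901 arm taken out, and g the number of points by which their month-6 change would have been worse than that of retained patients. With m the retained mean benefit, the mean over all randomized patients is (1 − x)·m + x·(m − g) = m − x·g. A comparison resting on retained patients therefore overstates the effect by x·g. The documents give neither x nor g; the ranges below are assumed.

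| x | g = 5 | g = 10 | g = 20 |
|---|---|---|---|
| 3% | 0.15 | 0.30 | 0.60 |
| 5% | 0.25 | 0.50 | 1.00 |
| 10% | 0.50 | 1.00 | 2.00 |
| 15% | 0.75 | 1.50 | 3.00 |

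These are values for a completers-type comparison. The mixed model also uses scores from before exit, so its shift may be smaller.

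**4. Precision, as illustration**

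With 182 randomized, difference 10 and SD 20, the t-test gives:

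- 30% of month-6 scores missing: about 127 evaluable, power 80%;
- 20% missing: about 146, power 85%;
- 10% missing: about 164, power 89%.

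How much of the 30% would come from these exits is not stated.

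**The case against.** The case against is substantial, and part of it stands.

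- **An AE is not a withdrawal criterion in 5.4.** Section 2.4 speaks of stopping the product for a known adverse reaction, 8.3.4 records drug withdrawal as an action taken for an AE, and the safety endpoints count treatment discontinuation due to AE. A patient who stops capsules for an AE is the case that the retention rule addresses. A reader might infer that the protocol instructs sites to remove such patients. It does not; it leaves room for it through criterion 3 and 5.6.
- **For medical conditions the two rules can be read together.** The criteria are permissive and the retention rule is qualified by feasibility. This stands, and it is why the conflict is called direct only for pregnancy.
- **Section 5.6 sets a safety duty.** It does not say that nothing else is followed. Likewise the bar on contact comes shortly after the text on consent withdrawal and may have been meant for those patients only, though its wording is not so limited. A synopsis that omits a sentence is abridged, not contradictory in itself.
- **The documents point to little difference in AEs.** Section 2.3.2 reports AE occurrence no higher than control, 42% against 40% of patients in the large stroke trial of the precursor product, and no serious events in the pilot. Section 2.4 does describe the commoner AEs as mainly gastrointestinal and possibly linked to capsule number. Loss related to arm is therefore possible, not shown.
- **Some data survive.** Earlier visits and the Early-Termination visit supply scores, and LOCF and per-protocol sensitivity analyses are planned. Neither recovers the month-6 value: LOCF carries an earlier score forward, and the per-protocol set drops the patient.

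**Conclusion.** The point holds as an inconsistency that should be fixed. It is not a flaw that must be cured before the trial can be interpreted. The protocol already states the right principle, but criterion 3, section 5.6 and the pregnancy passages are not aligned with it. The conflict is direct for pregnancy; for medical conditions and AEs the consequence is uneven site practice. Scores that are never collected cannot be restored by a later analysis plan.

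The size of any bias cannot be derived from the documents. The range of 0.15 to 3.0 points rests wholly on the assumed x and g. A reader might go further and infer an overstatement of 1 to 2 points (10 or 20% more of the MLC901 arm removed, all reverting to the placebo mean, so that a true 9 or 8 is reported as 10), or a power gain from 80% to 85% if a third of dropouts were retained. The arithmetic is correct, but the documents supply neither share, and 80% with 30% dropout is the planned design power, so the gain does not show a defect.

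**What to change.** 1. In 5.4, 5.6 and the synopsis, distinguish discontinuation of the IP from withdrawal from the study, and carry the retention sentence into the synopsis.
2. State that a patient who stops the IP for an AE or a medical condition, and has not withdrawn consent, is followed where possible at the remaining scheduled outcome visits, above all Visit 5.
3. Record the IP stop date and the study exit date as separate items, next to the reason for stopping that 5.4 already requires.
4. Reconcile criterion 3, and the pregnancy text in 5.4 and 8.3.1.2, with the retention rule. The clinical grounds for stopping, and whether study procedures continue in pregnancy, are for the sponsor to decide.

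The cost is minor wording changes and site retraining. The visits are already scheduled. The ITT estimate will contain somewhat more off-treatment data, which the retention rule already intends.
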